#### Analyses of secondary outcomes

4.1.4

We will analyze the effect of each condition on each physical health and mental health-related outcome. Hockberg's step-down procedure will be used to provide corrected and uncorrected *p*-values for the entire set of secondary outcomes [76]. To conduct these analyses by ITT, a slope will be fitted for each outcome variable across all time points. As before, these hypotheses will be tested using random regression models.

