### Overview

2.1

The currently proposed study is a community-based, pragmatic randomized-controlled trial. The aims of this study are to 1) test the impact of PlayFit, compared to Small Team Training (STT; i.e., group exercise), on cardiorespiratory fitness (i.e., VO_2peak_) and moderate-to vigorous-intensity physical activity (MVPA; self-reported and objectively monitored) after 6-and 12-months, and 2) examine group differences in rates of injury and PA program enjoyment and changes in self-efficacy, blood pressure, loneliness, anxiety, and depression. We hypothesize that participants randomized to both groups will improve their cardiorespiratory fitness similarly at month-6 (i.e., approximately 3.5 ml/kg/min), but those randomized to PlayFit will maintain these increases at month-12 through better attendance. Additionally, we hypothesize that changes in group attendance and cardiorespiratory fitness at month-12 will be mediated by group enjoyment. Finally, we hypothesize that participants randomized to PlayFit will demonstrate greater improvements in indices of physical health (i.e., blood pressure) and mental health-related (i.e., anxiety) outcomes compared to STT while reporting similar injury rates. All study procedures presented here have been approved by the Institutional Review Board (IRB).

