### Secondary dependent measures

2.4

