#### Mediators

2.4.1

All questionnaire-based measurements will be collected electronically using the Research Electronic Data Capture (REDCap [44]) system, a secure, web-based software platform.

**Physical activity enjoyment.** Participants will rate their perceived enjoyment of PA at baseline, 6, and 12-months using the Physical Activity Enjoyment Scale (PACES [45]), an 18-item questionnaire with 7-point bipolar scales where a higher score indicates greater perceived enjoyment. The stem, “Think about the exercise you have been doing…” is followed by items such as, “something I liked–something I disliked”. We will modify the stem to target specific enjoyment for the group to which the participant is assigned. (e.g., “Think about the exercise group you have been participating in during this study…"). The PACES has demonstrated excellent reliability in other adult samples [45].

**Exercise adherence.** Daily attendance logs will be maintained by the exercise leaders supervising each group.

**Self-reported physical activity.** Participants will self-report PA using the long-form of the International Physical Activity Questionnaire (IPAQ; [31]). The 31-item IPAQ was designed to provide an evaluation of PA in four domains: work, household, transportation, and leisure. A reference period of “during the last 7 days” will be used when collecting responses. The eight-day test-retest reliability for PA recall of the IPAQ was good with a median coefficient of *r* = 0.80. Criterion validity using accelerometers was acceptable with a median coefficient of 0.40 [46].

**Adverse events and injuries.** We will assess injuries and other adverse events monthly, using a self-report measure adapted from the one developed by Stathokostas and colleagues [47]. The questionnaire consists of 7-items that focus on the region of the body that is injured as well as the injury severity (i.e., whether the participant should contact or visit his or her PCP). Stathokostas and colleagues reported high test–retest reliability (*r* = 0.76) for this measure, with interrater agreement coefficients (*κ*) greater than 0.80.

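### The only stated rule for secondary outcomes fits a slope over time, but the injury aim is a comparison of rates, and a slope contrast cannot detect a constant rate difference

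*Protocol article*

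**What the plan says.** Section 2.1 (Overview) sets the second aim as to "examine group differences in rates of injury and PA program enjoyment and changes in self-efficacy, blood pressure, loneliness, anxiety, and depression". Injury and programme enjoyment are to be compared between groups, while the remaining measures are to be compared on change. The same section predicts that PlayFit will do better on physical and mental health measures "compared to STT while reporting similar injury rates".

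Injuries appear under section 2.4, headed "Secondary dependent measures", within subsection 2.4.1: "We will assess injuries and other adverse events monthly, using a self-report measure". No baseline injury value is described. Attendance is recorded in daily logs.

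Section 4.1.4 opens: "We will analyze the effect of each condition on each physical health and mental health-related outcome". It then applies a multiplicity procedure to the full set of secondary outcomes and states that "a slope will be fitted for each outcome variable across all time points", with hypotheses tested in random regression models as for the primary outcome. The article gives no other analysis for injuries.

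Section 4.1 (Sample size determination) expects similar adherence in the two arms up to month 6 and better adherence in PlayFit by month 12.

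**The concern.** The article separates rates from changes when it states its aims, then gives a single analysis rule built for change. That rule suits blood pressure or anxiety, which have a baseline and may drift. It does not suit injuries, which accrue from the start of the programme. If one programme injures more people in every month, the two monthly series lie at different heights but run parallel, and a comparison of slopes sees nothing.

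This is the trial's between-arm safety comparison, and the hypothesised result is similarity. A contrast with no power against the most obvious kind of difference leans towards the predicted answer. The slope can also respond to something else: if attendance diverges, monthly injuries per person diverge with it, even when a session is equally safe in both arms.

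**Working it through.** **Arm size.** The article gives no figure for injuries, so the 112 per arm planned for VO2peak is used. It reproduces. SD of change = √(36 + 36 − 2 × 0.39 × 36) = √43.92 = 6.627. Then n = 2 × (1.960 + 0.842)² × 43.92 / 2.5² ≈ 110.3, or 111 per group. With 112, power is 80.6% (normal) or 80.3% (t).

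**Why a slope misses a constant difference.** Let arm g have a constant expected count λ_g in months t = 1 to 12, with mean month 6.5. The expected least-squares slope is Σ(t − 6.5)λ_g / Σ(t − 6.5)² = λ_g × 0 / 143 = 0 in both arms, whatever the λ_g. A log link does not change this. In log λ = a + b·arm + c·t + d·arm·t, a constant rate ratio sits in b, and the slope contrast d is 0.

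**Simulation.** Assumptions: 112 per arm, 12 monthly reports, no dropout, gamma frailty with variance 0.5, rates constant over time, 2,000 trials per row, two-sided 0.05. Per-person slopes and means were compared by Welch t-test. The joint test was a 2-df Wald test. The table gives the percentage of trials that reject.

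| Injuries per person-month, two arms | Ratio | Slope only | Mean rate | Mean and slope jointly | Slope of cumulative count |
|---|---|---|---|---|---|
| 0.03, 0.03 | 1 | 4.8 | 5.1 | 4.4 | 4.9 |
| 0.03, 0.045 | 1.5 | 4.6 | 43.3 | 33.9 | 37.1 |
| 0.03, 0.06 | 2 | 5.1 | 90.0 | 83.5 | 85.3 |
| 0.05, 0.10 | 2 | 4.3 | 97.8 | 95.6 | 95.9 |
| 0.10, 0.20 | 2 | 4.6 | 99.9 | 99.6 | 99.7 |
| 0.05, 0.15 | 3 | 4.3 | 100 | 100 | 100 |

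The simulation error at 5% is √(0.05 × 0.95 / 2000) ≈ 0.5 percentage points, so the slope-only column cannot be told apart from the nominal level.

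**Where the result stops holding.**
- If both rates fall by 10% per month at a constant ratio of 2, the raw-count slope rejects in 21% (starting rates 0.05 and 0.10) to 39% (0.10 and 0.20). The arm with more injuries then shows the steeper decline, which could be misread as favourable.
- If injuries are taken at months 0, 6 and 12 with a shared zero at baseline, the slope rejects in 67% (0.03 and 0.06) to 86% (0.05 and 0.10).

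**Attendance.** Injuries per person-month = risk per session × sessions attended per month. With equal risk per session, a fall in STT attendance after month 6 lowers the STT injury rate and not the PlayFit rate. The slopes then differ although the sessions are equally safe.

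**The case against.** The strongest reply is that two steps are inferred. First, scope: section 4.1.4 opens with physical and mental health-related outcomes, section 2.1 illustrates these by blood pressure and anxiety and names injury apart from them, and section 2.4 is a mixed list that also holds attendance logs and body height. Second, the contrast: fitting a slope in a random regression model does not make the slope the only term tested. Such models normally carry a group term, and the mean-rate column shows that it would detect a doubling in 90% or more of trials. A cumulative count or a shared zero baseline would also pick it up.

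Both points stand, and they limit the claim. A reader might infer that the trial would declare similar injury rates almost regardless of the data, or that it would miss a doubling for certain. The documents do not support that: no passage makes the slope the sole test, and none says that a non-significant slope will be read as similarity. A count model, an exposure term and a similarity margin may also stand in an analysis plan that is not shown, so their absence is not held against the article.

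What survives is narrower. The one stated rule names only a slope and refers to every outcome variable, and the stated injury aim is a rate comparison. If injuries are outside the rule, the article gives that aim no analysis. Either way the text needs a sentence.

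It can also be said that the expected attendance divergence would make the injury slopes differ, so the slope is not blind. That is true, but what it would then detect is attendance.

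**Conclusion.** The point holds as a mismatch between a stated rule and a stated aim. On the literal reading, with the slope contrast as the test, a constant difference in monthly injury rate is found only at about the 5% false-positive rate, even when the rate is doubled or tripled. A direct comparison of rates finds the same doublings and triplings in 90% to 100% of trials.

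This rests on four conditions: injuries fall under section 4.1.4, the slope is the term tested, the counts are monthly and not cumulative, and the rates are constant over time. The injury rates and the over-dispersion are assumptions. The slope-only result hardly depends on them, because it follows from equal slopes. The power of the alternatives does depend on them, and falls to 43% for a ratio of 1.5 at the lowest rate. It is a fault worth correcting before analysis, and it does not affect the primary outcome.

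**What to change.** State in section 4.1.4 that injuries are not covered by the slope rule. Compare the arms as randomised by the 12-month injury rate ratio with a 95% CI, from a count model that allows over-dispersion (for example negative binomial), with the log of person-months of follow-up as offset. Base any statement that rates are similar on that interval, not on a non-significant p-value.

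A rate per attended session may be added from the attendance logs, but only as a supplementary, non-randomised description. Attendance arises after randomisation, the log of sessions is undefined for participants who attended none, and the questionnaire is not described as limited to session injuries. Restrict it to session-related injuries if these can be identified, and say how participants with no sessions are handled.

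The cost is one or two sentences, since the monthly reports and logs are already collected. The price is a wide interval if injuries are rare. With equal rates of 0.03 per person-month, each arm expects 112 × 12 × 0.03 ≈ 40 injuries. The SE of the log ratio is √[2 × (1/40.3 + 0.5/112)] ≈ 0.24, so an observed ratio of 1 has a CI of about 0.62 to 1.61. At 0.10 per person-month the same arithmetic gives about 0.74 to 1.35. That width is an honest picture of what the trial can say about similarity.

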#### Mediator analysis

4.1.5

We propose two potential mediators of fitness in the current study, perceived enjoyment and session attendance for each exercise group. We will examine these potential mediators using the analytical approach suggested by Baron and Kenny [77] and others [78]. Multiple regression analyses will be conducted to obtain the direct effects of the relationship between group assignment and fitness followed by examining the indirect effects of adding perceived enjoyment and attendance to the respective models.

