### Sample size determination

4.1

Our power and sample size calculations are based on the following considerations. First, studies among untrained adults have shown that supervised group exercise can increase VO_2peak_ by approximately 4 ml/kg/min over 12 months [[64], [65], [66]]. Based on data derived from the National Health and Nutrition Examination Survey (NHANES) among men (*mean*_VO2peak_ = 42.1 ml/kg/minute) and women (*mean*_VO2peak_ = 34.2 ml/kg/minute) 30–39 years of age [67], we assume the baseline VO_2peak_ of participants will be approximately 35.0 (SD = 6.0). The SD of 6.0 is a conservative estimate using data from the Naval Research Lab, where it was 6.3 and 3.9 in men and women, respectively [68]. After 6-months, we anticipate that participants in both PlayFit and STT will improve their VO_2peak_ by approximately 10% (i.e., 3.5 ml/kg/min), owing to similar rates of program adherence. However, after 12-months, we anticipate only those randomized to PlayFit will maintain these changes in cardiorespiratory fitness, due to better program adherence. These differences in adherence will lead to a maintained improvement (versus baseline) in VO_2peak_ of PlayFit participants at 12-months of 3.5 ± 6.0 ml/kg/minute versus 1.0 ± 6.0 for STT. In this case, sample sizes of 112 in each group achieve 80% power to detect a mean difference of 2.5 ml/kg/minute with a standard deviation of 6.0 at the first time point, a standard deviation of 6.0 at the second time point, a two-sided significance level (*α*) of 0.05, and a correlation between measurements of 0.39. To account for participant attrition, we will oversample at a rate of 25%. Therefore, we will recruit up to 280 participants for the proposed study.

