#### Preliminary data analysis plan

4.1.1

Given the relationship between cardiorespiratory fitness and mortality [69], we will conduct the primary analysis on changes in fitness. First, to ensure successful randomization, the two groups will be examined for homogeneity. If it is determined that the groups differ significantly on any variable, we will include those variables as covariates in subsequent analyses. For the primary outcome (VO_2peak_), we will apply intention-to-treat (ITT) principles with all available data included in the first set of analyses [70,71], with the assumption that participants who are lost to follow-up will not have changed their level of fitness since their last observation.

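### The mediation regressions in section 4.1.5 name no mediator-outcome confounders, and the only covariate rule responds to imbalance between arms, so the indirect effect is biased if baseline fitness is related to enjoyment or attendance

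*Protocol article*

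**What the plan says.** Section 4.1.5 names the two mediators ("We propose two potential mediators of fitness in the current study, perceived enjoyment and session attendance for each exercise group") and the method: "We will examine these potential mediators using the analytical approach suggested by Baron and Kenny [77] and others [78". The regressions are meant "to obtain the direct effects of the relationship between group assignment and fitness followed by examining the indirect effects of adding perceived enjoyment and attendance". The section names no baseline variable and does not say whether fitness enters as the month-12 level or as change from baseline.

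The only rule for choosing covariates is in section 4.1.1: "If it is determined that the groups differ significantly on any variable, we will include those variables as covariates in subsequent analyses". It covers all later analyses, so it reaches the mediation models.

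Section 2.5 is headed as dealing with covariates. It lists exercise self-efficacy, preference for group exercise, competitiveness and sociodemographic items, but no analysis section assigns them to a model.

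Mediation is a stated hypothesis. The Abstract says so, and section 2.1 reads: "we hypothesize that changes in group attendance and cardiorespiratory fitness at month-12 will be mediated by group enjoyment".

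**The concern.** Randomisation protects the comparison of arms on the mediator and on fitness. It does not protect the path from mediator to fitness, because participants are not randomised to enjoy the sessions or to attend them. Within either arm, people who start fitter may enjoy the sessions more, attend more, and be fitter at month 12 for reasons unrelated to enjoyment or attendance.

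The rule in section 4.1.1 looks at a different question. It asks whether the arms differ, whereas this confounding is present even when the arms are perfectly balanced. If balance is tested at 0.05 (the article gives no level), the rule would admit baseline VO2peak in about 5% of randomisations. Age group and sex are randomisation strata (section 3.2) and so are balanced by design; the rule would rarely select them.

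What is at stake is the trial's explanation of its result, namely whether enjoyment and attendance carry the effect of PlayFit on fitness.

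**Working it through.** **1. The plan's own figure.** Section 4.1 gives a difference of 2.5 ml/kg/min, "a standard deviation of 6.0 at the first time point, a standard deviation of 6.0 at the second time point", "a correlation between measurements of 0.39", two-sided alpha 0.05 and 80% power.
- SD of change = 6.0 × √(2 × (1 − 0.39)) = 6.63.
- n per group = 2 × (1.960 + 0.842)² × 6.63² / 2.5² ≈ 110.3, so 111. At 112 per group, power is 80.3% (noncentral t).
- 112 × 1.25 = 140 per arm, 280 in total.

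The sample size reproduces and does not depend on this point.

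**2. Inputs for the bias.**
- From the article: r = 0.39 between baseline and month-12 VO2peak; SD = 6.0; 112 per arm; total effect 2.5.
- Assumed: within-arm correlation ρ between baseline VO2peak and the mediator of 0.1, 0.2 or 0.3 (0.4 as an extreme); arm effect on the mediator a = 0.5 SD.

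**3. Expected indirect effect when the true one is zero.** With arm and mediator in the model but not baseline VO2peak, and the mediator in SD units:
- Month-12 level: a × ρ × r × SD = 0.5 × ρ × 0.39 × 6.0.
- Change: a × ρ × (r − 1) × SD = 0.5 × ρ × (−0.61) × 6.0.

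The sign turns because baseline correlates negatively with change: (0.39 − 1)/√(2 × 0.61) = −0.55.

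| ρ | Level (ml/kg/min) | Change (ml/kg/min) |
|---|---|---|
| 0 | 0 | 0 |
| 0.1 | +0.12 | −0.18 |
| 0.2 | +0.23 | −0.37 |
| 0.3 | +0.35 | −0.55 |

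Against the planned 2.5, this is about 5% to 14% (level) or 7% to 22% (change, in size).

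**4. How often mediation is declared when none exists.** Simulation with 112 per arm and 4,000 trials per setting; mediation is declared when both the arm-to-mediator and mediator-to-fitness paths have p < 0.05.

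| ρ | Level | Change (opposite sign) | Baseline VO2peak in model |
|---|---|---|---|
| 0.1 | 8% | 13% | 4% |
| 0.2 | 21% | 36% | 5% |
| 0.3 | 39% | 68% | 5% |

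Independent reruns gave 9%, 19% and 40% for level, and 12%, 37% and 67% for change.

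**5. What happens to true mediation.** True indirect effect 0.50 ml/kg/min, 2,000 trials per setting. Detection means both paths significant with a positive indirect effect.

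| ρ | Level: mean estimate | Change: mean estimate | Change: detected | Baseline-adjusted: mean estimate | Baseline-adjusted: detected |
|---|---|---|---|---|---|
| 0 | 0.50 | 0.51 | 60% | 0.50 | 75% |
| 0.2 | 0.73 | 0.12 | 7% | 0.51 | 74% |
| 0.3 | 0.81 | −0.09 | 1% | 0.51 | 74% |
| 0.4 | 0.89 | −0.32 | 0% | 0.50 | 69% |

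The level analysis exaggerates mediation and the change analysis hides it. Baseline adjustment recovers the true value in each setting.

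**6. Sensitivity to the arm effect.** With a = 0.8 SD and ρ = 0.3, the bias when nothing is mediated is +0.55 (level) or −0.88 (change). At ρ = 0 it is absent whatever a is.

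**The case against.** **The text is silent, not exclusive.** A reader might infer that the regressions contain only arm, enjoyment and attendance. Section 4.1.5 does not say so. It lists no covariates and excludes none, the mediators may enter one per model, section 4.1.1 would add any imbalanced variable, and section 2.5 labels several variables as covariates. A condensed article may also leave the covariate list to a fuller plan. This stands as a limit on the wording. It does not dispose of the point, because the article does fix a method and a selection rule, and that rule cannot address within-arm confounding.

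**The change-score rates are not false support for the hypothesis.** Sections 2.1 and 4.1.1 both speak of changes in fitness. A reader might take the 13% to 68% as the trial wrongly confirming its explanation. Those results have a negative indirect effect, which contradicts the hypothesis. Counting only the hypothesised direction, false mediation under change is 0.4%, 0.0% and 0.0% at ρ = 0.1, 0.2 and 0.3. This stands: under change, the harm is masking.

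**The level rates depend on the definition of mediation.** Requiring a significant total effect as well gives 7%, 19% and 36%. Requiring the direct effect also to become non-significant gives 1%, 5% and 9%. This is fair, but the bias in the estimate is the same under any of these definitions.

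**The key correlation is assumed.** No section gives a correlation between baseline fitness and either mediator, or the arm effect on the mediator. All participants are sedentary, and PlayFit is self-paced and made easier to play, which could weaken the link. On the other side, the article's own theory ties competence to enjoyment. It also says that women attend group classes more than men (section 3.2.2) and reports lower VO2peak in women (section 4.1). A confounder is therefore plausible but not shown, and its direction need not be the one modelled here.

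**Conclusion.** The concern holds in a limited form. As described, the mediation analysis leaves the non-randomised mediator-to-fitness path without confounder adjustment unless a variable happens to differ between arms. Under the assumed ρ of 0.1 to 0.3 and a 0.5 SD arm effect on the mediator, the bias is about +0.1 to +0.35 ml/kg/min for the month-12 level, with false mediation in about 8% to 40% of trials. For change it is about −0.2 to −0.55, mainly hiding true mediation. Section 4.1.5 leaves open which form of fitness applies, and so leaves the sign open.

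The documents do not show that such bias will occur, since it vanishes at ρ = 0. Nor do they support extending the point to the randomised comparison of VO2peak or to the sample size, both of which are unaffected. The change is worth making because mediation is a stated hypothesis and the remedy is cheap.

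**What to change.** In section 4.1.5:
- Include baseline VO2peak, age and sex in every mediator model and every outcome model, whatever the arm balance. All three are already collected, and age group and sex are the randomisation strata.
- Add baseline exercise self-efficacy and preference for group exercise where these are measured before randomisation; section 2.5 does not give their timing.
- State the outcome as month-12 VO2peak adjusted for baseline.
- Do not rely on baseline PACES with the group-specific stem. Section 2.4.1 rewords it to refer to the assigned exercise group, and no such group exists before randomisation, so it cannot measure the same construct then.
- Say that the rule in section 4.1.1 does not decide the covariates of the mediation models.

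The cost is wording, a few model terms and a few degrees of freedom out of about 224 analysed participants (2 × 112). No new visits or participants are needed. Adjustment removes only the part due to the measured covariates. Unmeasured confounding can remain, and the report should say so.

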## Abstract

Despite the myriad benefits associated with regular physical activity (PA), few American adults accrue sufficient weekly PA. Although “lack of time” is often cited as a correlate of physical inactivity, a growing body of evidence suggests that, perhaps more importantly, people allocate their leisure-time to activities they find more enjoyable than PA. These findings underscore the need to devise physical activities that will be chosen over other enjoyable, but less healthy, behavioral alternatives. As a first step in this direction, we designed a group social PA play program for adults, known as PlayFit. The overarching philosophy of PlayFit is that fun and enjoyment are among the most important influences on PA adherence. In PlayFit, traditional sport games are modified to fulfill basic psychological needs, in a non-competitive, and non-contact environment. We will randomize 280 sedentary adults 18–50 years of age to 12-months of PlayFit or traditional group exercise, matching the groups on intensity, frequency, and duration. The primary outcomes include cardiorespiratory fitness (VO_2peak_), group adherence, and group enjoyment. We hypothesize that, at 6 months, cardiorespiratory fitness will have increased to the same extent in both groups, but at 12 months, only those randomized to PlayFit will have maintained their fitness through better adherence than Group Exercise – and this outcome will be mediated by enjoyment of the assigned group. Findings from this study could provide evidence that a focus on providing fun and enjoyable PA experiences for adults may be a viable route toward improving PA adherence. A simple, inexpensive PA intervention, such as PlayFit, may represent one such approach to do so.

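### The mediator analysis calls the total effect of group on fitness a direct effect, and the Baron and Kenny steps it names would lose power if a significant total effect is required first

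*Protocol article*

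**What the plan says.** Section 4.1.5 (Mediator analysis) of the protocol article names the candidates: "We propose two potential mediators of fitness in the current study, perceived enjoyment and session attendance for each exercise group". It gives the method as follows: "We will examine these potential mediators using the analytical approach suggested by Baron and Kenny [77] and others [78". It then describes multiple regressions "to obtain the direct effects of the relationship between group assignment and fitness followed by examining the indirect effects of adding perceived enjoyment and attendance".

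Mediation is a stated hypothesis of the trial. The Abstract expects PlayFit alone to hold its fitness gain at 12 months and adds that "this outcome will be mediated by enjoyment of the assigned group". Section 2.1 (Overview) repeats the idea: "we hypothesize that changes in group attendance and cardiorespiratory fitness at month-12 will be mediated by group enjoyment".

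The comparison that a mediation analysis would start from is sized in section 4.1 (Sample size determination). It assumes a change in "VO_2peak_ of PlayFit participants at 12-months of 3.5 ± 6.0 ml/kg/minute versus 1.0 ± 6.0 for STT", and states that "sample sizes of 112 in each group achieve 80% power to detect a mean difference of 2.5 ml/kg/minute".

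**The concern.** There are two separate points.

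**Label.** A regression of fitness on group, without mediators, estimates the total effect. The direct effect is the group coefficient after the mediators are added. The indirect effect is the product of the group-to-mediator and mediator-to-fitness coefficients. Section 4.1.5 puts the group-fitness relation first, calls it direct, and brings in the mediators afterwards. A report that followed this wording would present the whole treatment effect as the part that does not pass through enjoyment or attendance.

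**Method.** In its classical form, the Baron and Kenny approach asks first for a significant group-outcome relation and then judges mediation from a chain of tests. The mediation claim then inherits the power of the primary comparison. It loses more if the true fitness difference is below 2.5, even when both links of the mechanism are real.

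The stake is the explanatory claim of the trial: that enjoyment is what keeps PlayFit participants fit. The primary fitness comparison itself is not touched.

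**Working it through.** **1. Reproduce the plan's own figure.** Inputs from section 4.1: SD 6.0 at both time points, correlation 0.39, difference 2.5 ml/kg/min, two-sided alpha 0.05, 112 per group.

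- SD of change = √(36 + 36 − 2 × 0.39 × 36) = 6.627.
- Standardised difference = 2.5 / 6.627 = 0.377.
- The normal approximation needs 111 per group. At 112 per group, power is 0.806 (normal) or 0.803 (noncentral t).

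The stated 112 per group and 80% power are confirmed. A test of the total effect therefore fails in about one trial in five when every planning assumption is true.

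**2. Upper bound under a gate.** If mediation is declared only when the total effect and both paths are all significant, the probability of that joint event cannot exceed the probability of the first. At the planned effect the bound is about 80%.

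**3. Size of the loss, by simulation.** The documents give no mediator path sizes, so these are assumptions. *a* is the group effect on the mediator in SD units. *b* is the mediator-to-fitness slope in SD units. There is one mediator, 112 per arm, and an SD of change within arm of 6.627. *With gate* means that the total effect and both paths are significant. *Without gate* means that both paths are significant.

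Total effect 2.5 (as planned):

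| Assumed paths | With gate | Without gate | Loss (points) |
|---|---|---|---|
| strongest: *a* = 0.5, *b* = 0.3 | 78% | 96% | 18 |
| *a* = 0.5, *b* = 0.15 | 46% | 58% | 12 |
| *a* = 0.3, *b* = 0.3 | 52% | 61% | 9 |
| weakest: *a* = 0.3, *b* = 0.15 | 30% | 37% | 7 |

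Total effect 1.5, over the same four pairs: about 17-39% with the gate against 37-96% without it.

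**4. Check with an actual interval and stronger paths.** A second simulation used a Monte Carlo 95% interval for the indirect effect, a group-to-mediator effect of 0.5 to 0.8 SD, and 50% to 100% of the total effect mediated. At a total of 2.5, power was 77-80% with the gate and 95-100% with the interval. In 17-20% of trials the interval excluded zero while the total effect was not significant. The interval and the test of both paths gave nearly the same power (for example 0.9695 and 0.9655), so the table is a fair guide to what an interval would deliver.

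**5. What the label does to the numbers.** With *a* = 0.5 and *b* = 0.3, the indirect effect is 0.5 × 0.3 × 6.627 = 0.99 ml/kg/min, and the direct effect is 2.5 − 0.99 = 1.51. With *a* = 0.3 and *b* = 0.15, they are 0.3 × 0.15 × 6.627 = 0.30 and 2.20. In both cases the model without mediators estimates 2.5, which the wording of section 4.1.5 would call direct.

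**The case against.** **No gate is written down.** Section 4.1.5 does not say that the mediators are examined only after a significant group difference, and it cites other work alongside Baron and Kenny. That second source is not available here and may supply an estimate and interval for the indirect effect. This stands. A reader might infer that a real indirect effect is missed whenever the overall fitness difference is not significant. The document does not support that: the loss follows only if the classical steps are applied.

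**No test or interval is stated.** A reader might also take this silence as a defect. A condensed article commonly leaves such detail to the full protocol or the analysis plan, so the silence alone is no finding. What remains is what the section does state: the named method and the label.

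**A significant total effect may suit this hypothesis.** The Abstract and Overview speak of explaining a difference at 12 months; without a difference there is little to explain. This has force, and the choice is partly one of estimand. It argues for careful wording when an indirect effect appears without a total effect. It does not argue for withholding the estimate.

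**The power figures rest on assumed paths.** This is correct. With the weakest pair, power is 37% even without the gate, so path strength then limits power more than the gate does. A total of 1.5 also departs from the planning assumption, and section 4.1.5 plans two mediators where the simulation has one. The direction is the same in every case examined; the size is not fixed.

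**The label is only wording.** Both models would be fitted whatever they are called, so the coefficients can be recovered. This is also correct, but the wording decides which number is reported as which effect.

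**Conclusion.** The concern holds in a limited form. On the natural reading, section 4.1.5 gives the name of the direct effect to a model that estimates the total effect. This needs no assumption about the data. The section also commits to an approach that, applied classically, caps power to declare mediation at about 80% when the planned difference is true. Over the assumed range of paths, the cost is about 7 to 18 points at a difference of 2.5. It is larger at 1.5: about 39% against 96% at the strong end, and 17% against 37% at the weak end. These sizes depend on a gate that the text does not state, on path strengths that the documents do not give, and on a single-mediator model. The issue affects the explanatory analysis only; the sample size and the primary comparison stand.

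**What to change.** Rewrite section 4.1.5, and the matching text of the analysis plan, to define three quantities for month-12 VO2peak:

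- total effect: the group coefficient without mediators;
- direct effect: the group coefficient with the mediators in the model;
- indirect effect: the product of the group-to-mediator and mediator-to-fitness coefficients.

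Base inference on a 95% percentile-bootstrap or Monte Carlo interval for the indirect effect, and state that a significant total effect is not required. Stop using the term direct effects for the model without mediators. If the second cited source already provides such an interval, say so; correcting the label then settles the point.

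The cost is a paragraph of text and standard software, with no extra data or participants. The small downside is that an indirect effect found without a significant total effect must be reported as such, and not as the explanation of a demonstrated fitness difference.
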